### Outcome measures

#### Primary outcomes

1. Number of recurrent thrombotic events between those with raised D-dimer at point of randomisation who were randomly allocated to the treatment arm (group RW) and those with raised D-dimer at point of randomisation who were randomly allocated to the no treatment arm and produced a normal D-dimer off treatment (NRO) and those with raised D-dimer at point of randomisation who were randomly allocated to the no treatment arm and then produced a raised D-dimer off treatment (RRO) (see Figure 1)

**Figure 1 F1:**
[figure not shown]
Flow chart for trial intervention.

2. Number of recurrent thrombotic events between those showing an elevated D-dimer off treatment (RO) versus those showing a negative D-dimer off treatment (NO) (see Figure 1)

#### Secondary outcomes

1. Severity of PTS between groups

2. Bleeding events - defined as in Table 2

3. INR control in terms of percentage time in range

4. Optimal cut off on a D-dimer result

5. Costs of D-dimer and subsequent extended treatment with anticoagulation

6. Cost effectiveness

7. Information on the types of patient who potentially benefit from extended warfarin treatment, age and gender

8. Patient quality of life

**Table 2 T2:** Definition of bleeding events

**Major bleeding**	Clinically overt bleeding that is associated with:
	A fall in haemoglobin of 2 g/dl or more, or
	A transfusion of 2 or more units of packed red blood cells or whole blood, or
	A critical site: intracranial, intraspinal, intraocular, pericardial, intra-articular, intramuscular with compartment syndrome, retroperitoneal, or
	A fatal outcome
**Non-major clinically relevant bleeding**	Non-major clinically relevant bleeding is defined as overt bleeding not meeting the criteria for major bleeding but associated with medical intervention, unscheduled contact (visit or telephone call) with a clinician, (temporary) cessation of warfarin treatment, or associated with discomfort for the subject such as pain or impairment of activities of daily life.
	Examples of non-major clinically relevant bleeding are:
	• Epistaxis if it lasts for more than 5 minutes, if it is repetitive (i.e., 2 or more episodes of true bleeding, i.e., not spots on a handkerchief, within 24 hours), or leads to an intervention (packing, electrocautery, etc.) and no admission to hospital.
	• Gingival bleeding if it occurs spontaneously (i.e., unrelated to tooth brushing or eating), or if it lasts for more than 5 minutes
	• Haematuria if it is macroscopic, and either spontaneous or lasts for more than 24 hours after instrumentation (e.g., catheter placement or surgery) of the urogenital tract
	• Macroscopic gastrointestinal haemorrhage: at least 1 episode of melena or hematemesis, if clinically apparent
	• Rectal blood loss, if more than a few spots
	• Haemoptysis, if more than a few speckles in the sputum, or
	• Intramuscular hematoma
	• Subcutaneous hematoma if the size is larger than 25 cm^2^ or larger than 100 cm^2^ if provoked

### Ascertainment of outcomes

#### D-dimer results

All baseline and six monthly D-dimer results will be recorded onto the trial database by practice staff.

#### Thrombotic events and associated deaths

• At six monthly intervals and at the end of the study patient GP records will be reviewed for any mention of hospital admission, to ascertain any thrombotic events including fatalities, and whether they are still taking warfarin.

• When hospitalisation or death is identified in the study population, a discharge summary and a copy of the death certificate (if applicable) will be obtained. (The patients’ NHS numbers will be flagged at the Medical Research Information Service to inform on cause of death).

• These will be scrutinised by the Independent Adverse Event committee who will be blinded to the treatment allocation. The committee will decide what was the primary cause of hospitalisation/death. This committee will meet once all the data has been collected.

• Research nurses will abstract other information concerning the hospital admission, including admission and discharge dates, and discharge destination. Date of death will be recorded.

Recurrence will need to be objectively documented (i.e. defined radiologically). Radiological criteria for recurrent DVT will be: a new non-compressible venous segment compared to the examination at baseline; an increase of 4 mm or more in thrombus diameter with compression; or, a convincing extension in length.

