### Participants

Patients will be recruited through a number of primary care and secondary care anticoagulation clinics in the wider Midlands area over a two year period.

Patients identified as receiving warfarin for a first unprovoked proximal DVT or PE and who are eligible for the trial (Table 1) will receive a brief information sheet about the study during their anticoagulant clinic appointment. They will also be given a post card to return to the research department stating their willingness in principle to take part in the study, for their GP to be contacted and their records to be accessed for the purpose of checking their eligibility for the study. The patients GP will simultaneously be sent a summary of the trial and informed that one of their patients wishes to participate. The GP will be asked to complete a form to state whether they wish their practice to take part in the study.

**Table 1 T1:** Study inclusion and exclusion criteria

**Inclusion criteria**	People aged 18 years or over with a diagnosis of first unprovoked^*^ proximal^** ^DVT or PE on treatment with anticoagulants
	Have completed 3 – 6 months of anticoagulant therapy (target 2–3)
	^*^The episode will be defined as unprovoked as long as there is no history within the previous 3 months of:
	major surgery; lower limb trauma e.g. fracture, cast, limping for 3 days; use of the combined oral contraceptive pill or hormone replacement therapy ; pregnancy; significant immobility e.g. confined to bed for 3 days; active cancer.
	^**^Proximal refers to a DVT alone in the trifurcation area, popliteal, superficial femoral, deep femoral, common femoral and iliac veins.
**Exclusion criteria**	Patients under the age of 18 years
	Patients with another indication for long term warfarin therapy e.g. Atrial Fibrillation
	Patients with a diagnosis of first unprovoked proximal DVT or PE who are no longer on anticoagulation therapy
	Patients with a high risk of bleeding as evidenced by any of the following:
	• Patients with a previous episode of major bleeding where the cause was not effectively treated
	• Known thrombocytopaenia with a platelet count of less than 120 ×10^9^ /L
	• Known chronic renal failure with a creatinine of more than 150 μmols/L (1.7 mg/dl) or eGFR less than 30
	• Known chronic liver disease with a total bilirubin of more than 25μmols/L (1.5 mg/dl)
	• Active peptic ulcer
	• Patients requiring antiplatelet therapy (eg Aspirin and/or Clopidogrel)

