### Trial intervention

Study participants will have a total of six visits over a two year period.

#### Visit 1

This is the same visit as the information, consent and randomisation visit and will be within 2 weeks of current anticoagulation treatment end date. Patients will be randomised electronically into one of two groups; Group O will discontinue warfarin after their usual clinical intervention, Group W will continue warfarin for a further two years.

Patients will be interviewed to collect the following data:

Concomitant medications; ethnicity; smoking status; alcohol consumption; medical history; BMI; and family history of VTE

A heparinised venous sample of blood will be taken for a D-dimer test on a POC device (Cobas h 232, Roche diagnostics). In addition citrated venous samples will be collected for D-dimer testing. These will be sent to a central laboratory to be frozen and stored for analysis during and at the end of the study.

The D-dimer result will be recorded centrally onto a database for future analysis and both patient and researcher will be blinded as to the result of this test.

All patients will be clinically examined for signs and symptoms of PTS using a validated clinical scoring system (the Villalta scale) and will also complete the VEINES quality of life score [24] as well as EQ 5D which allows the measurement of broad aspects of quality of life [25]. In addition the patients will complete a costs questionnaire relating to the expenses incurred on a recent anticoagulation clinic visit. Where questionnaires are incomplete or unclear the patients will be contacted by telephone to clarify and complete the responses.

Compression stockings will be used by patients as advised by the clinician treating the DVT and the researchers will not influence their utilisation.

The anticoagulation clinic that the patient would normally attend will be informed that the patient is entering a study as will any specific hospital consultants who are involved with the patients’ care (e.g. haematologists). Patients randomly allocated to Group W will be followed-up through their usual oral anticoagulation service provided in terms of warfarin management and the anticoagulation clinic lead will be asked to extend their clinic visits for a further 2 years. Patients randomly allocated at this point to Group O will undergo a further D-dimer test 1 month after cessation of treatment. Again both researcher and patient will be blinded to this result.

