#### Visits 2–6

All patients randomised (Groups W and Group O) will be reviewed every 6 months for 2 years in total to assess evidence of VTE recurrence, clinical assessment of PTS, and measurement of D-dimer (again patient and researcher are blinded to these results).

All patients will again be asked to complete the VEINES-QOL/Sym a validated disease specific, quality of life score, and EQ 5D, questionnaires.

If a patient in Group O (off warfarin) has their warfarin restarted by their GP during the study period for a VTE recurrence then they will be removed from the study but a case review will be carried out in patient’s primary care notes looking for evidence of thrombotic events. If a patient in Group O has to restart warfarin for another reason e.g. atrial fibrillation, then they will continue to be followed up in the usual manner. If a patient in Group W (on warfarin) has to permanently stop taking their warfarin during the study then they will be followed up and included in the final analysis on an intention to treat basis. If a patient in Group W has a temporary break in their treatment for any reason, they will continue to follow the same visit regime, making a note of the temporary break.

Patients in Group W will be asked to return for a final D-dimer test 1 month after discontinuing warfarin.

Patients randomised into group W will continue with their warfarin management as before. INR data will be collected from the anticoagulation database at six monthly intervals throughout the study to assess overall control.

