### Randomisation

Randomisation will be performed within the computerised clinical case report form (CRF) produced in Primary Care Clinical Sciences, University of Birmingham. When a patient is identified as being eligible for the study and has given written consent to take part, the research nurse will enter details into the computerised CRF and will be issued immediately with a dedicated randomisation code allocating the patient to either continuing warfarin therapy or stopping warfarin therapy.

Patients will be randomly allocated at this point to either continue warfarin (Group W) for a further 2 years or to discontinue treatment (Group O). Randomisation will be stratified by DVT and PE to ensure there are equal numbers in both groups W and O.

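### The radiology-only recurrence rule leaves out fatal PE established without imaging, and its first DVT criterion relies on a baseline scan that no listed visit supplies

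*Protocol article*

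**What the plan says.** Both primary outcomes in the protocol article (Primary outcomes) are numbers of recurrent thrombotic events, so the definition of recurrence decides what is counted. That definition is in Ascertainment of outcomes, Thrombotic events and associated deaths, which does three things.

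- It casts a wide net. GP records are reviewed "to ascertain any thrombotic events including fatalities". For admissions and deaths, discharge summaries and death certificates are obtained and passed to an independent committee, blinded to allocation, which decides the main cause.
- It sets the rule for what counts: "Recurrence will need to be objectively documented (i.e. defined radiologically". No exception is made for deaths.
- It gives three alternative criteria for recurrent DVT. The first is "a new non-compressible venous segment compared to the examination at baseline". The other two are "an increase of 4 mm or more in thrombus diameter with compression; or, a convincing extension in length". Only the first names a comparator.

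The visit descriptions under Trial intervention include no leg imaging. The examination at Visit 1 is clinical: "All patients will be clinically examined for signs and symptoms of PTS using a validated clinical scoring system". The later visits are "to assess evidence of VTE recurrence, clinical assessment of PTS, and measurement of D-dimer". On timing, Table 1 requires that patients "Have completed 3 – 6 months of anticoagulant therapy (target 2–3". Patients whose index event was PE are enrolled and form a stratum: "Randomisation will be stratified by DVT and PE to ensure there are equal numbers in both groups W and O".

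**The concern.** The section looks for fatal events in sources that often hold no imaging, appoints a committee to judge them, and then applies a counting rule that cannot admit what the committee finds unless a scan exists. The effect is to lose the most serious form of the primary event, or to leave the committee to decide after the fact whether the rule binds it.

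The DVT criterion has a related weakness. *Baseline* is not defined for imaging, and no listed visit produces a leg scan. Two committees could classify the same DVT differently, and the uncertainty is greater for patients who entered with PE and may never have had a leg scan.

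At stake are the completeness and reproducibility of a primary endpoint expected to contain few events.

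**Working it through.** **1. Fatal events: the two statements side by side.**

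- Ascertainment: fatal thrombotic events are sought from GP records, discharge summaries and death certificates, and the blinded committee assigns cause.
- Counting: recurrence must be objective, and the *i.e.* in the rule equates objective with radiological.

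Take a death that autopsy shows, or the committee concludes, was due to PE, with no scan before death. It is found by the first statement. It fails the second, although autopsy proof is objective. Nothing in the article says that the committee's attribution overrides the rule. A fatal PE that was imaged before death is unaffected.

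**2. The DVT comparator: two readings of baseline.**

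D-dimer results, in the same part of the article, uses *baseline* for trial entry. The other reading is the diagnostic scan of the index event, which precedes 3–6 months of treatment.

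| Case | Baseline = trial entry | Baseline = index diagnostic scan |
|---|---|---|
| Segment reopens on treatment, then clots again | Would be new, but no entry scan is listed | Not new under criterion 1; may still qualify on diameter or length, whose comparator is not named |
| DVT after index PE, no earlier leg scan | No comparator | No comparator; could be read as new or as indeterminate |

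So criterion 1 may fail or be impossible to apply. Failure of all three criteria does not follow.

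**3. Scale, from the article's own figures (Sample size).**

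Inputs: 79 per group, 2-year rates 21.4% and 4.3%, 90% power, 5% test (two-sided reproduces the figure); 316 completers, so 158 per arm; 14.2% in Group O and 1.4% to 4.3% in Group W.

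Reproduction, pooled-variance formula without continuity correction: n = [1.960 × √(2 × 0.1285 × 0.8715) + 1.282 × √(0.214 × 0.786 + 0.043 × 0.957)]² / 0.171² = 78.4, so 79. Power at 79 is 90.2%. Overall W versus O power at 158 per arm is 86.3% to 99.1%, matching the stated 86 to 99%.

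Expected events:

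- Main raised-D-dimer comparison: 79 × 0.214 = 16.9 untreated and 79 × 0.043 = 3.4 on warfarin, about 20.3 in all. One event is 1/20.3 = 4.9% of the total.
- Whole arms: 158 × 0.142 = 22.4 in Group O; 158 × 0.014 = 2.2 to 158 × 0.043 = 6.8 in Group W.

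The share of true recurrences that the rule would miss is not in the documents. Purely as an illustration, assume the same share is lost in both groups of the main comparison:

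| Share missed (assumed) | Power at 79 per group |
|---|---|
| 0% | 90.2% |
| 5% | 88.4% |
| 10% | 86.4% |
| 20% | 81.4% |
| 30% | 75.3% |

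An equal proportional loss leaves the risk ratio at 21.4/4.3 = 5.0. It reduces only the event count, the absolute difference and the power.

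**The case against.** The best reply is that a search net wider than the endpoint definition is normal, not contradictory. Records are searched to find candidates, and the radiological rule then selects among them. That is fair as far as it goes, and it means the article does not promise to count deaths on a certificate alone. What stands is that the rule, as worded, gives the committee no route to count a VTE death it is satisfied about unless there was imaging. That is a stated rule producing a worse endpoint, not a missing detail.

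The second reply is that a journal article condenses. The full protocol or a committee charter may define the baseline scan, cover index-PE patients and give imaging criteria for recurrent PE. This stands for the absence of a PE imaging criterion, which is not part of this point. It weakens the comparator point without removing it: the article does name a comparator, and its own visit schedule does not supply one. Table 1 defines DVT by named proximal veins, which implies that diagnostic imaging exists for the DVT stratum, so the index scan is a workable reading there.

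A reader might infer that re-thrombosis of a reopened segment, or any DVT after an index PE, cannot meet the recurrence rule. The documents do not support that. The three criteria are alternatives, two name no comparator, a re-clotted vein may be wider or longer, some PE patients may have had leg scans, and a first non-compressible segment can be read as new.

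A reader might also infer a bias between arms. The rule is the same in both arms and randomisation is stratified by index event, so no such bias follows.

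**Conclusion.** The point holds in two parts of unequal weight.

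The main part is the fatal events. Taken literally, the radiological requirement leaves out of the primary endpoint a fatal PE established at autopsy or by the committee without imaging, although the same section sets out to find such deaths. This rests only on the article's wording.

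The lesser part is the comparator. It is either absent or the diagnostic scan from before treatment, so some DVTs may fail criterion 1 or be unclassifiable. This assumes that no leg scan is done beyond the visits listed and that the full protocol does not settle the matter.

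The size cannot be derived from the documents. Unimaged fatal PE is likely to be a small share of recurrences. With about 20 events expected in the main comparison, even one or two misclassified events would be noticeable, but the power figures above are conditional on an assumed share. They should not be read as an estimate of loss, not least because the article does not say which recurrence definition lay behind its planning rates. It is a correction to endpoint wording, not a threat to the design.

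**What to change.** In Thrombotic events and associated deaths:

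1. State that the blinded committee may count a VTE death as a recurrence on autopsy or clinical record, and add a sensitivity analysis limited to events confirmed by imaging.
2. Replace the undefined baseline examination with the existing diagnostic leg scan of the index event, and say that any later scan report also goes to the committee. Making the latest available scan the comparator is less attractive: for anyone not rescanned it is still the index scan, and in a trial where patients and clinicians know who stopped warfarin, rescanning could differ by arm.
3. State that where no earlier leg scan exists, the committee decides, blinded to allocation, whether a symptomatic proximal non-compressible segment is new.
4. Add existing scan reports to the documents collected for the committee, since only discharge summaries and death certificates are named at present.

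The cost is endpoint wording and retrieval of reports that already exist. No scan is added and no treatment changes. The downside is some committee judgement on unimaged deaths and on patients without an earlier scan. The sensitivity analysis shows how far results depend on the unimaged deaths; recording which DVTs were judged without an earlier scan would let the same be shown for those.

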#### INR control

Patients INR results, with the amount of warfarin taken, will be collected onto the trial database at 6 months, 18 months and at the end of the study.

#### Patient quality of life

This will be assessed by all patients completing questionnaires at each study visit.

Veines-QOL/Sym a validated disease specific quality of life questionnaire will be used as well as EQ-5D allows changes in health status to be measured but also valued, using the University of York Measurement & Valuation of Health general population survey tariff. Where questionnaires are incomplete or unclear the patients will be contacted by telephone to clarify and complete the responses.

#### Incidence and severity of PTS

Measured using a validated clinical scoring system (the Villalta scale). Signs will be measured on both legs [26].

#### Cost data

The cost analysis will adopt a broad perspective to include costs incurred within the health sector and by patients. Health sector costs will include additional costs of D-dimer testing and prolonged treatment (anticoagulation) costs. Patient level data will be collected on treatment and condition-specific health service utilisation (primary and secondary care), thrombotic episodes, PTS and bleeding events. Information on costs incurred by patients when attending anticoagulation clinics (e.g. time and travel costs) will also be collected with a patient cost questionnaire. Information on resource use will be collected from patient notes. Unit costs will be obtained from standard sources and health care providers.

### Sample size

Initially, patients will be randomly assigned to warfarin (Group W) or no treatment (Group O) arms Following the flow chart for analysis (Figure 1) will result in 6 study populations, those with normal D-dimer at point of randomisation who were randomly allocated to the warfarin treatment arm (group NW), those with elevated D-dimer at point of randomisation who were randomly allocated to the treatment arm (group RW), those with normal D-dimer at point of randomisation who were randomly allocated to the no treatment arm and then produced a normal D-dimer off treatment (NNO), those with normal D-dimer at point of randomisation who were randomly allocated to the no treatment arm and then produced an elevated D-dimer off treatment (RNO), those with elevated D-dimer at point of randomisation who were randomly allocated to the no treatment arm and produced a normal D-dimer off treatment (NRO) and those with elevated D-dimer at point of randomisation who were randomly allocated to the no treatment arm and then produced an elevated D-dimer off treatment (RRO). (Thus in the two or three letter code the last letter indicates the arm a patient is randomised to, the previous letter indicates the outcome of the D- dimer test performed on the same visit as randomisation and, in the case of those randomised to no further treatment, the first letter relates to the D-dimer result produced after randomisation). A 10% loss to follow up rate is assumed from the beginning of the trial. The Data Safety Monitoring Board will inform the research team if recruitment is below target as the study progresses and if so further hospitals will be recruited.

Total sample size will be sufficiently large to show a significant difference in recurrence rates between those showing a positive D-dimer on treatment who receive warfarin (RW) and those showing a positive D-dimer who receive no treatment (RNO plus RRO). Following Palareti [7] this means a sample size for each group of 79 in order to give 90% power to a 5% significance test when comparing 2 year recurrence rates of 21.4% and 4.3%. Assuming a 50% positive D-dimer rate this implies a total of 79 × 2 × 2/0.9 = 352 patients taking part in the study (and 316 completing the study). Allowing a 50% participation rate this means that 704 patients need to be approached initially. With such a sample size an overall comparison of recurrence rates between the arms W and O can be made with power of between 86 and 99% assuming recurrence rates of between 1.4% and 4.3% for the warfarin arm (Group W, depending on what recurrence rate patients with normal D-dimer on warfarin produce) and 14.2% for the No treatment arm.

One of the objectives of the study is to determine an optimal cut off on a D-dimer result taken when the patient is receiving treatment. In a study of 272 patients, Baglin *et al.* report that 170/272 patients had a D-dimer in excess of 500 ng mL-1 and their ROC analysis suggests an optimal cut off of 500 ng/ml [10]. The circumstances of their study differ from ours but using their data will give some indication of the precision with which we will be able to estimate an optimal cut off with slightly more patients than Baglin *et al.* With some assumptions, a rough calculation of the precision with which a cut off in the region of 500 could be estimated with our sample size of 316 would be within about 7% (95% confidence interval).

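### The 99% upper power for W versus O rests on a 1.4% warfarin-arm recurrence rate that the plan's own inputs rule out

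*Protocol article*

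**What the plan says.** All the figures stand in the Sample size section of the protocol article. The trial is sized on patients with a raised D-dimer, with 79 per group to give "90% power to a 5% significance test when comparing 2 year recurrence rates of 21.4% and 4.3" per cent, the lower rate being for those on warfarin. "Assuming a 50% positive D-dimer rate", the total becomes "352 patients taking part in the study (and 316 completing the study").

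The section then turns to all of Group W against all of Group O. It reports "power of between 86 and 99% assuming recurrence rates of between 1.4% and 4.3% for the warfarin arm" and 14.2% for the no-treatment arm. A parenthesis attributes the width of the Group W range to one unknown: how often patients with a normal D-dimer recur while on warfarin. No figure is given for that unknown.

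**The concern.** A whole-arm rate is a weighted average of the rates in its two D-dimer halves. The paragraph fixes one half at 4.3% and lets only the other vary. A whole-arm rate of 1.4% lies below what the fixed half contributes by itself, so no value for the other half can produce it.

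This matters because the Abstract gives prevention of recurrence by extended treatment as the primary aim, and this sentence holds the only power quoted for the overall W versus O comparison. If its favourable end comes from an impossible event rate, a reader relying on that end is relying on power the design does not have.

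**Working it through.** **Inputs, all from the protocol article**

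- Raised D-dimer share: 50% (Sample size).
- Two-year recurrence with raised D-dimer: 4.3% on warfarin, 21.4% off (Sample size).
- Group O overall: 14.2%. Group W overall: 1.4% to 4.3% (Sample size).
- Completers: 316 after a 10% loss (Sample size). The Randomisation section stratifies "to ensure there are equal numbers in both groups W and O", so 316/2 = 158 per arm.
- Significance level 5%. Sidedness is not stated; two-sided reproduces the plan's 79 per group.

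**Step 1. Reproduce the plan's figures.** The pooled normal sample-size formula for 21.4% versus 4.3% at 90% power gives 79 per group, and 79 × 2 × 2/0.9 = 351.1, rounded up to 352. For W versus O, with d the difference in rates and p̄ their mean,

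power = Φ{ [d√n − 1.96√(2p̄(1−p̄))] / √(p_O(1−p_O) + p_W(1−p_W)) }, with n = 158 and p_O = 0.142.

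- p_W = 4.3%: (0.099 × 12.570 − 1.96 × 0.4097)/0.4037 = 1.093, power **86.3%**.
- p_W = 1.4%: (0.128 × 12.570 − 1.96 × 0.3793)/0.3683 = 2.350, power **99.1%**.

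Both ends match the plan, so 1.4% was used as the rate for the whole of Group W.

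**Step 2. Is 1.4% possible?** Write NW for the rate in normal-D-dimer patients on warfarin.

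- Group W rate = 0.5 × 4.3% + 0.5 × NW.
- Floor, at NW = 0: 0.5 × 4.3% = **2.15%**.
- NW needed for 1.4%: 2 × 1.4% − 4.3% = **−1.5%**.
- Alternatively, even with NW = 0, the raised share would have to be at most 1.4/4.3 = 32.6%, against the 50% used to reach 352.

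**Step 3. Power at rates that are possible**

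| Group W rate | NW implied | Power | Chance of missing the effect |
|---|---|---|---|
| 4.3% (stated) | 4.3% | 86.3% | 13.7% |
| 2.85% | 1.4% | 95.4% | 4.6% |
| 2.15% (floor) | 0% | 97.7% | 2.3% |
| 1.4% (stated) | −1.5% | 99.1% | 0.9% |

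**Step 4. Where 1.4% may come from (inference).** Group O's 14.2% is a feasible average: 2 × 14.2% − 21.4% = 7.0% in its normal-D-dimer half. Scaling that by the warfarin ratio in raised-D-dimer patients gives 7.0% × 4.3/21.4 = 1.4%. This suggests that a subgroup rate was entered as the arm rate. With NW = 1.4%, the arm rate is (4.3% + 1.4%)/2 = 2.85%.

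**Step 5. Sensitivity to method.** At the 2.15% floor with 158 per arm, other calculations give 96.3% (continuity-corrected), 98.0% (unpooled), 98.1% (Fisher), 98.9% (arcsine) and 98.9% (exact chi-square). The last two come close to 99%, but at 4.3% they give 88.4% and 88.2%, so they do not reproduce the plan's 86%.

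**The case against.** The strongest reply is that nothing in the design depends on this figure. The sample size was set by the raised-D-dimer comparison, and both listed primary outcomes compare D-dimer subgroups. The main Discussion also says that the study chiefly concerns patients with raised D-dimer. W versus O is offered as a comparison that the resulting size happens to allow, and the cautious end of its range, which shows adequacy, is correct. All of this stands, and it limits the weight of the point.

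A second reply concerns the replacement figure. A reader might infer that the consistent range is 86% to 95% and that the chance of a missed effect at the favourable end is 4.6%. The documents do not establish that. They give no normal-D-dimer rate on warfarin, no 7.0% rate off warfarin, and no statement that warfarin's relative effect is the same in both D-dimer strata. The numerical match in Step 4 makes the reading plausible, but it remains a reconstruction. The inputs as written allow any normal-D-dimer rate from 0% upward, so the supported ceiling is 97.7%.

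Neither reply rescues the 1.4%, which contradicts two figures in the same paragraph.

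**Conclusion.** Wrong as written, and minor. Given the 50% share and the 4.3% rate, Group W cannot recur at less than 2.15%, so the 99% has no feasible assumption behind it. The attainable range is 86.3% to at most 97.7%, an overstatement of 1.3 points at the upper end (99 − 97.7). If 1.4% was meant as the normal-D-dimer rate, the upper figure is 95.4% and the overstatement is 3.6 points (99 − 95.4).

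These figures assume 158 completers per arm, an even D-dimer split within Group W, 14.2% in Group O and a two-sided 5% pooled normal test, the method that reproduces the plan's own numbers.

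A reader might go further and conclude that the trial is underpowered or wrongly sized. That does not follow: the 86% lower end, the 79 per group, the 352 enrolled and the 316 completing are all unaffected.

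**What to change.** In the Sample size section, state the recurrence rate assumed for normal-D-dimer patients on warfarin, compute the Group W rate as its 50:50 average with 4.3%, and restate the upper power from that rate. If the assumed rate is 1.4%, the Group W range becomes 2.85% to 4.3% and the power about 86% to 95%. Whatever rate is chosen, the upper figure should not exceed about 98% under the plan's method. The authors need to confirm which rate they intended; 1.4% should not be written in as the subgroup rate on the strength of the arithmetic alone.

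The cost is one sentence and a slightly less favourable figure. Recruitment targets and the design do not change.
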